### Stepped-care programme

Participants in the intervention group are offered a stepped-care programme. All participants are offered step 1. Participants who still report elevated levels of psychological distress after step 1 (i.e. score > 15.9 on the K10 at *t*_2_) are also offered step 2.

#### Step 1: Doing What Matters in times of stress (DWM)

The DWM web app consists of five modules with accompanying audio exercises corresponding to each of the five chapters of the SH + self-help book: (1) grounding, (2) unhooking, (3) acting on your values, (4) being kind, and (5) making room. Each week, a new module unlocks. Based on Step-by-Step, a guided e-mental health intervention [53], participants receive a total of six weekly 15-min support calls from a non-specialist (lay) helper *(see ‘*Helpers*’)*: one welcome call, and a total of five follow-up calls – one at the end of each module. During these calls, the previous module(s) and exercise(s) are discussed and participants have the opportunity to ask questions. Helpers have also limited access to participants’ metadata, such as if a participant has logged into the web app and when they finished a module. Additionally, the web app has a chat support system through which participants can chat with their helper at the weekly support moment in case they are unable to have a phone call.

#### *Step 2: Problem Management Plus (PM* +*)*

PM + teaches four strategies: (1) stress management, (2) problem solving, (3) behavioural activation, and (4) strengthening social support, and has a psycho-education component [27]. PM + is delivered over five weekly sessions with a non-specialist (lay) helper *(see ‘*Helpers*’)*. For this project, PM + has been adapted to be delivered in individual 60 (instead of 90) minute video-call sessions (MS Teams). Before implementation of the stepped-care interventions, a qualitative sub-study is performed to assess the main daily-life problems and psychosocial care needs of IMWs in the Netherlands, to contextually adapt both interventions [76]. Data collected for this qualitative assessment is conducted following Module 1 of the Design, Implementation, Monitoring and Evaluation (DIME) research model, which consists of free listing interviews, key-informant interviews with both IMWs and professionals and a focus group discussion [77]. Core elements of the interventions remained the same, while case examples and pictures were adapted. Details of this adaptation process will be published elsewhere.

#### Helpers

Helpers are Polish migrants living in the Netherlands. Participants are linked to a helper who delivers all calls in DWM or all sessions in PM + . For participants who continue to PM + , this may be the same helper as they had for DWM, but this is not necessary. Helpers delivering the DWM support calls and PM + sessions will be Polish people living in the Netherlands. They have been trained in the intervention by mental health professionals, who themselves have been trained by so-called Master trainers in both the intervention and the supervision process.

Training of trainers (ToT) was online and consisted of a two-day DWM and a five-day PM + training (August–September 2021). Training of helpers (ToH) was hybrid and consisted of a two-day DWM and an eight-day PM + training (January-March 2022). Throughout the trial, helpers will receive weekly online supervision by these trainers. Trainers will receive online supervision by the Master trainers on an as-needed basis.

#### Treatment fidelity

Treatment fidelity will be assessed in various ways. First, helpers will fill in a session checklist after each DWM call and PM + session, and supervisors do so after each supervision. Second, 10% of the recordings of the DWM phone calls and PM + sessions will be assessed with fidelity checklists. This will be done for a random sample, stratified on helpers for DWM and PM + separately. Fidelity checks take place throughout the delivery of the programme, resulting in an iterative process of programme monitoring informing programme delivery. Third, metadata on participants’ app usage, e.g. if a participant has completed a module, will be collected.

### Care-as-usual (CAU)

CAU refers to all (mental) health care available to IMWs, both in and outside the Netherlands. IMWs become eligible for (mental) health care in the Netherlands upon signing up for health insurance, which is mandatory for all residents as well as those subject to payroll tax. They can access health care by registering with a general practitioner. No aspect of care will be altered or withheld as a result of participation in this study.

## Analysis

### Sample size

We aim to detect a small-to-medium Cohen’s *d* effect size of 0.3 on the PHQ-ADS composite score (primary outcome) at the *t*_*4*_ follow-up assessment point, which is based on previous RCTs on PM + [28, 29]. Power calculations suggested a minimum sample size of 74 per group (power = 0.95, α = 0.05, two-sided). With an expected 30% attrition at *t*_*4*_, we aim to include 212 study participants (intervention group: *n* = 106, control group: *n* = 106) over an 18-month inclusion period.

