## Methods

### Study aim and design

This study is part of the EU Horizon2020 RESPOND project, which aims to improve the preparedness of European mental health care systems in the face of future pandemics. The primary objective of the current study is to evaluate the (cost-)effectiveness, feasibility, and acceptability of the culturally and contextually adapted DWM/PM + stepped-care program among Polish migrant workers living in the Netherlands throughout the COVID-19 pandemic in terms of mental health outcomes, resilience, wellbeing, and costs to health systems and society. This will be done by conducting a single-blind, two-arm, parallel-group, superiority RCT with a 1:1 allocation ratio in which a remotely delivered stepped-care programme with PFA and care-as-usual (enhanced care-as-usual or eCAU) will be compared to PFA with CAU (eCAU) only. The primary endpoint is a composite measure of depression and anxiety at 21 weeks from baseline assessment (*t*_4_). Figure 1 shows a flowchart of the study design. In addition, we will explore barriers and facilitators to treatment engagement and adherence and opportunities for scaling up among IMWs in the Netherlands, as well as the implementation outcomes of the stepped-care programme. This will be done by a mixed-methods process evaluation following the RCT.

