#### Quantitative data (RCT)

Intention-to-treat (ITT) and per-protocol (PP) analysis will be conducted for both the primary and secondary outcomes. ITT analysis will include all randomized participants (*N* = 212). PP analysis will include participants in the intervention group only if they have (a) clicked through at least three (out of five) modules of the DWM web application, and (b), if they qualified for PM + in terms of K10-distress score at *t*_2,_ attended at least four (out of five) PM + sessions. ITT analysis of the primary outcome will be used to answer the main research question.

To compare differences between the two treatment groups at baseline, t-tests (continuous variables) and chi-squared tests (categorical variables) will be conducted for normally distributed data. For continuous non-normally distributed data, Mann–Whitney tests will be conducted.

To estimate the treatment effect on the primary outcome at *t*_2_, *t*_3_, and *t*_4_, with *t*_4_ being our primary time point of interest, a linear mixed model will be used. This model will have time and treatment as fixed effects (as well as their interaction parameters), a baseline measure of the PHQ-ADS as a covariate, and subjects as random effects. The mean difference between the two treatment groups at each assessment with a 95% confidence interval will be obtained from this mixed model. The same linear mixed model will be used to estimate the effect of the DWM/PM + stepped-care programme on secondary outcomes: symptoms of depression (PHQ-9), anxiety (GAD-7), PTSD (PCL-5), quality of life (EQ-5D-5L), and an outcome-based resilience variable, operationalised as the PHQ-ADS total score against stressor exposure [78].

Missing data will not be imputed but will be treated as missing at random (MAR) as linear mixed models can handle missing data. If some items of a particular scale are missing (i.e. < 50%), the Corrected Item Mean Substitution method will be used [79]. This method uses the item mean across participants of the same study group and time point, weighted by the subject’s mean of completed items. All the above-mentioned analyses will be performed using Jamovi version 2.3.26 [80]. Jamovi is an open-source graphical user interface for R.

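### 74 per group does not give 95% power for d = 0.3 at week 21: the stated inputs give about 44% unadjusted, and 55–72% with baseline adjustment at correlations of 0.5 to 0.7

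*Protocol article*

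**What the plan says.** The Sample size section of the protocol article sets the target: "We aim to detect a small-to-medium Cohen’s *d* effect size of 0.3 on the PHQ-ADS composite score (primary outcome"), at the t4 follow-up. It gives the error rates as "power = 0.95, α = 0.05, two-sided" and the result as "Power calculations suggested a minimum sample size of 74 per group". It then allows for 30% loss at t4 and arrives at 106 per group, 212 in total. It states no correlation, number of repeated measurements or other variance-reducing factor.

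Study aim and design describes a "two-arm, parallel-group, superiority RCT with a 1:1 allocation ratio". The Primary outcome measure section fixes week 21 (t4) as the endpoint. The quantitative part of Data analysis specifies a linear mixed model with treatment, time, their interaction and baseline PHQ-ADS as a covariate, and adds: "The mean difference between the two treatment groups at each assessment with a 95% confidence interval will be obtained from this mixed model". The effect to be tested is therefore the baseline-adjusted difference between groups at t4.

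**The concern.** For a two-group comparison, d = 0.3 is a small-to-medium effect, and 95% power is a demanding target. Together they normally call for several hundred participants per group, so 74 looks too small by a factor of about four.

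The claimed power is the main operating characteristic of the primary comparison. If it is 95%, a true effect of 0.3 would be missed 5% of the time. If it is 44–55%, the trial would miss that effect about as often as it finds it (56% of the time unadjusted, 45% at r = 0.5). A non-significant t4 result carries very different weight in the two cases.

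**Working it through.** **Inputs from the article.** d = 0.3 (PHQ-ADS at t4), two-sided alpha 0.05, power 0.95, 1:1 allocation, 74 per group evaluable, 30% attrition, 106 per group randomised.

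**Assumption, not in the article.** The baseline–t4 correlation r, taken over a range. Adjusting for baseline multiplies the outcome variance by (1 − r²). d is taken in units of the unadjusted SD.

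**1. The attrition step reproduces.** 74 / (1 − 0.30) = 105.7, so 106 per group and 212 in total. The 74 is thus the evaluable number, and the discrepancy arises before this step.

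**2. Sample size from the stated inputs.** n per group = 2(z₀.₉₇₅ + z₀.₉₅)²(1 − r²)/d².

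- r = 0: 2 × (1.960 + 1.645)² / 0.09 = 288.8, so 289 (290 with the noncentral t).
- r = 0.5: 288.8 × 0.75 = 216.6, so 217 (noncentral t: 218).
- r = 0.6 and 0.7 (noncentral t): 186 and 149.

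Other readings of the error rates do not give 74 either. One-sided 95% power needs 241, two-sided 90% needs 234, two-sided 80% needs 175 and one-sided 80% needs 138 per group.

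**3. Power at d = 0.3.** The noncentrality is 0.3 × √(n/2) / √(1 − r²). For n = 74 and r = 0 it is 0.3 × √37 = 1.825, against a critical t of 1.976 on 146 df.

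| r | Power, 74 per group | Power, 106 per group |
|---|---|---|
| 0 | 44% | 58% |
| 0.5 | 55% | 71% |
| 0.6 | 62% | 78% |
| 0.7 | 72% | 86% |
| 0.8 | 86% | 95% |

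**4. What 74 per group can detect with 95% power.** Unadjusted, d = 0.597. With adjustment this becomes 0.597 × √(1 − r²): 0.52 at r = 0.5 and 0.43 at r = 0.7. To bring it down to 0.3, √(1 − r²) must equal 0.3 / 0.597 = 0.503, so r ≈ 0.86.

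**5. Expected precision with 74 per group.** The 95% confidence interval half-width is 1.976 × √(2/74) ≈ 0.32 SD unadjusted, and 0.32 × √0.75 ≈ 0.28 SD at r = 0.5.

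**6. A possible origin of 74 (inferred; the article does not state it).** A repeated-measures within-between interaction calculation with f = 0.15, two groups, two measurements and correlation 0.5 first passes 95% at N = 147. Rounded to equal groups this is 148, or 74 per group, with power 0.952. There, f = 0.15 stands for a between-group difference in change of 4 × 0.15 = 0.6 SD. The noncentrality agrees: √(0.15² × 148 × 2 / 0.5) = 3.65, and 0.6 × √37 = 3.65. A difference of 0.3 SD corresponds to f = 0.075, and the same calculation then returns 44%.

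**The case against.** **The planned analysis adjusts for baseline.** This is correct, and it makes 44% the least favourable figure for that analysis. The article condenses a fuller protocol that may state a correlation. But only a value of about 0.86 reconciles 74 with 95% power, which is very high for symptom scores about 20 weeks apart with treatment in between.

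**The mixed model uses repeated measures and all randomised participants.** Among people with t4 data, the t2 and t3 values add almost nothing to the t4 contrast. People seen at t2 or t3 but not at t4 do contribute under missing at random, so the completer figures are a lower bound. The 106-per-group column is the upper bound, and it reaches 95% only at r of about 0.8 with no loss at all. Averaging the three follow-ups would be a different estimand. With all correlations equal and 74 per group it would still give only about 81% (r = 0.5) or 91% (r = 0.7).

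**The article already plans a confidence interval.** That is so, and it limits the harm. No section says that non-significance will be taken as absence of effect.

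**Stronger readings that the article does not support.** A reader might infer that the authors entered the wrong effect size in a repeated-measures routine. The numerical match is suggestive, but the settings are nowhere stated and the finding does not need them. A reader might also infer that true power is simply 44%, or that 95% is impossible. Neither follows, because an undisclosed correlation of about 0.86 would deliver it.

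**Conclusion.** The power statement is wrong as written: 74 per group, d = 0.3, two-sided 5% and 95% power are mutually inconsistent, and no other section supplies an input that reconciles them. For r from 0 to 0.7, power is about 44–72% with 148 completers and at most 58–86% if nobody is lost. The stated power fits an effect of about 0.60 (r = 0) down to 0.43 (r = 0.7), between about 1.4 and 2 times the named target.

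The unadjusted figures and the inconsistency rest only on the article's own inputs. The adjusted figures depend on the assumed correlation. The finding concerns the stated operating characteristic; it does not invalidate the design, the analysis model or the randomised comparison.

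**What to change.** Keep N = 212 and correct the Sample size paragraph, by amendment or published correction, so that it:

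- names the test as the baseline-adjusted between-group contrast at t4, and states the assumed baseline–t4 correlation and its basis;
- states that 148 completers give about 44–72% power for d = 0.3 over r = 0 to 0.7, noting that partial follow-up may add something to this;
- states that 95% power applies to d of about 0.60 (r = 0) down to 0.43 (r = 0.7);
- commits to interpreting the t4 result by its 95% confidence interval, and not reading non-significance as no effect.

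If the full protocol does contain a correlation that yields 74, it should be printed with its source. The change costs one paragraph of text and no extra participants, which matters because the Trial status section already reports 138 enrolled. The downside is that the stated power becomes less favourable.

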### Data analysis

Data will be analyzed once all data has been collected; no interim analyses will be conducted.

#### Quantitative data (RCT)

Intention-to-treat (ITT) and per-protocol (PP) analysis will be conducted for both the primary and secondary outcomes. ITT analysis will include all randomized participants (*N* = 212). PP analysis will include participants in the intervention group only if they have (a) clicked through at least three (out of five) modules of the DWM web application, and (b), if they qualified for PM + in terms of K10-distress score at *t*_2,_ attended at least four (out of five) PM + sessions. ITT analysis of the primary outcome will be used to answer the main research question.

To compare differences between the two treatment groups at baseline, t-tests (continuous variables) and chi-squared tests (categorical variables) will be conducted for normally distributed data. For continuous non-normally distributed data, Mann–Whitney tests will be conducted.

To estimate the treatment effect on the primary outcome at *t*_2_, *t*_3_, and *t*_4_, with *t*_4_ being our primary time point of interest, a linear mixed model will be used. This model will have time and treatment as fixed effects (as well as their interaction parameters), a baseline measure of the PHQ-ADS as a covariate, and subjects as random effects. The mean difference between the two treatment groups at each assessment with a 95% confidence interval will be obtained from this mixed model. The same linear mixed model will be used to estimate the effect of the DWM/PM + stepped-care programme on secondary outcomes: symptoms of depression (PHQ-9), anxiety (GAD-7), PTSD (PCL-5), quality of life (EQ-5D-5L), and an outcome-based resilience variable, operationalised as the PHQ-ADS total score against stressor exposure [78].

Missing data will not be imputed but will be treated as missing at random (MAR) as linear mixed models can handle missing data. If some items of a particular scale are missing (i.e. < 50%), the Corrected Item Mean Substitution method will be used [79]. This method uses the item mean across participants of the same study group and time point, weighted by the subject’s mean of completed items. All the above-mentioned analyses will be performed using Jamovi version 2.3.26 [80]. Jamovi is an open-source graphical user interface for R.

As an exploratory additional analysis, digital markers will be assessed using open-source tools in a Python environment, which is available on GitHub [38, 74]. Digital markers will be assessed using open source tools in a Python environment, which is available on GitHub [38, 74]. Change over time in digital markers will be calculated using repeated measures analysis of variance (ANOVA). A covariate mixed model of the primary endpoint will be conducted by adding relevant covariates at baseline, including gender, age, education, migration and work characteristics (e.g. duration of stay, type of contract), relationship status, living situation, life events, traumatic experiences, COVID-19-related events. An exploratory analysis will also be conducted to see if steroid hormone levels and baseline and between-session change in digital markers are associated with treatment recovery.

To determine the cost-effectiveness of the DWM/PM + stepped-care programme, health economic analysis will be conducted from a healthcare system and societal perspective. This will be conducted by focusing on the incremental cost per quality-adjusted life year (QALY, based on the EQ-5D-5L) and per change in PHQ-ADS composite score at the *t*_*4*_ follow-up assessment point (week 21). To do so, the total cost of the delivery of the intervention and changes in the uptake of health care will be assessed, using the CSRI. Between-group comparison of mean costs will be conducted using appropriate statistical tests, depending on the type and distribution of data. Univariate sensitivity analysis will be conducted using non-parametric bootstrapping to estimate the uncertainty and variability on trial parameters, which will be addressed by constructing cost-effectiveness planes and acceptability curves.

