#### Screening measures

Psychological distress will be measured with the K10 [47]. The K10 consists of ten items that focus on anxiety and depression-related distress over the past 30 days. Items are scored on a five-point Likert scale (1–5), giving a total score of 10–50 with higher scores representing higher levels of distress. In line with previous research [48, 49] a cut-off score of > 15.9 is used, which indicates psychological distress [50]. The K10 is validated in various languages (e.g. Dutch) [51].

 Suicidal ideation will be assessed with the suicidal thoughts interview from the PM + manual (*t*_0_*,* screening) [52] or with a screening question used in a previous trial testing an e-health intervention (*t*_2_-*t*_4_) [53]. If a participant answers positively to this screening question (*t*_2_-*t*_4_), a message will appear with information on where to get help and stating that a member of the research team will reach out to the participant. Once a phone call has been scheduled with the participant, an assessor will administer the suicidality module of the Mini-International Neuropsychiatric Interview (MINI) [54]. Suicidal ideation is not assessed during *t*_1_ as this directly follows screening. Cognitive impairment will be assessed with the observation checklist from the PM + manual.

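### The per-protocol rule screens only the intervention arm, and screens those still distressed at t2 harder, so the per-protocol contrast tends to favour the programme even with no effect

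*Protocol article*

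**What the plan says.** All statements are in the protocol article.

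- Quantitative data (RCT), on the DWM condition: "PP analysis will include participants in the intervention group only if they have (a) clicked through at least three (out of five) modules". Those whose t2 K10 made them eligible for PM+ must in addition have "attended at least four (out of five) PM + sessions". No per-protocol criterion is stated for the control group.
- Stepped-care programme: step 2 goes to "Participants who still report elevated levels of psychological distress after step 1", defined as K10 > 15.9 at t2. Screening measures uses the same threshold for entry: "a cut-off score of > 15.9 is used, which indicates psychological distress".
- Quantitative data (RCT): intention-to-treat and per-protocol "analysis will be conducted for both the primary and secondary outcomes". The mixed model has "a baseline measure of the PHQ-ADS as a covariate, and subjects as random effects"; distress at t2 is not a covariate.
- The same section gives intention-to-treat precedence: "ITT analysis of the primary outcome will be used to answer the main research question".

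**The concern.** Take two intervention participants who each completed three modules. The one at or below the cut-off at t2 stays in the per-protocol set. The one still above it stays only after at least four PM+ sessions. A control who is equally distressed at t2 stays in without condition. The rule thus thins out distressed participants in one arm only, using a score measured after randomisation and related to the outcome.

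This goes beyond the usual worry that adherent participants have a better prognosis. It operates even if attendance has nothing to do with prognosis. At stake is the reading of the per-protocol results for the primary and secondary outcomes: a per-protocol estimate larger than the intention-to-treat estimate could be taken as evidence that fuller participation brings more benefit, when the selection rule produced some or all of the gap.

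**Working it through.** The protocol states no figure for the per-protocol set, so there is none to reproduce. The yardstick is its target of d = 0.3 on PHQ-ADS at t4 (Sample size).

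**From the protocol:** the two conditions, the K10 threshold, no control criterion, adjustment for baseline PHQ-ADS, 106 per arm, 30% attrition at t4.

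**Assumed:** true effect zero; share s above the cut-off at t2, 0.50-0.85; PM+ completion a, 0.50-0.85; DWM completion 0.70; correlation r of K10 at t2 with PHQ-ADS at t4, 0.4-0.7; correlation of baseline with each later score 0.5; normal scores; completion unrelated to outcome in the base case. DWM completion then thins both t2 groups equally and cancels. Negative values favour the programme.

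**1. Share still distressed in the intervention set** = s·a / [(1 − s) + s·a]. With s = 0.7, a = 0.5: 0.35 / (0.30 + 0.35) = 0.54, against 0.70 in controls.

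**2. Shift in mean t2 K10** (SD units): m = −(1 − a)·φ(c) / [(1 − s) + s·a], with c = Φ⁻¹(1 − s). For s = 0.7, φ(c) = 0.348. With a = 0.5, m = −0.5 × 0.348 / 0.65 = −0.268.

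**3. Baseline-adjusted bias at t4** ≈ (r − 0.5 × 0.5)·m. The simulated values come from 400,000 participants per arm.

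| s | a | r | formula | simulated |
|---|---|---|---|---|
| 0.7 | 0.5 | 0.5 | 0.25 × −0.268 = −0.067 | −0.069 |
| 0.7 | 0.5 | 0.7 | 0.45 × −0.268 = −0.121 | −0.119 |
| 0.7 | 0.7 | 0.7 | 0.45 × −0.132 = −0.059 | −0.061 |
| 0.5 | 0.5 | 0.7 | 0.45 × −0.266 = −0.120 | −0.126 |
| 0.85 | 0.85 | 0.5 | 0.25 × −0.040 = −0.010 | −0.011 |

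At r = 0.4 the smallest case (s = a = 0.85) is 0.15 × −0.040 = −0.006. The range is therefore about −0.01 to −0.13 SD. Against the target, the simulated extremes are 0.011/0.3 = 4% and 0.126/0.3 = 42%.

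**4. Which condition causes it.** If everyone who steps up completes PM+ (a = 1), m = 0. The simulated bias is then −0.005 to +0.002 SD and the two-sided error 4.6-5.6%. The PM+ condition is the source.

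**5. Error rates.** In 2,000 simulated trials per setting (106 per arm, 30% attrition, a < 1, r of 0.5 or 0.7), false findings in favour of the programme were 2.4-10.0%, against a nominal 2.5%.

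**6. Check with a mixed model** (random intercept, t2-t4, baseline covariate, r = 0.6, s = 0.7, 200 trials each): −0.050 SD at 70% PM+ completion and −0.100 SD at 50%, with Monte Carlo standard errors of about 0.012 and 0.013.

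**7. When attendance depends on outcome** (r = 0.6, s = 0.7; log-odds of PM+ completion per SD of worse outcome):

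| log-odds | a = 0.5 | a = 0.7 |
|---|---|---|
| −0.5 | −0.193 | −0.119 |
| 0 | −0.088 | −0.047 |
| +0.25 | −0.046 | −0.012 |
| +0.5 | −0.006 | +0.012 |
| +1.0 | +0.061 | +0.057 |

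**The case against.** **Intention-to-treat is primary.** The protocol says so outright and gives the per-protocol analysis no decision weight. This stands. A reader might infer that the trial's conclusion is compromised; the document does not support that.

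**A conditional adherence rule is natural.** Step 2 is offered only above the cut-off, so adherence to a stepped programme has to be defined conditionally. This is a fair defence of the definition of adherence. It does not justify using that definition to drop participants from one arm and then comparing the remainder with all controls.

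**The size can be overstated.** A reader who simulates baseline-adjusted residuals can reach 0.16 SD, about half the target. But d = 0.3 is stated on the PHQ-ADS score and the rule uses the K10 score; on those scales the same setting gives about 0.12 SD. The largest values also combine low PM+ completion with a high correlation.

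**The direction is not certain.** Step 7 shows it cancelling or reversing if the more distressed attend clearly more often. This stands.

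**Missing t2 K10.** A reader might infer that someone with three modules and no t2 K10 never qualified for PM+ and so counts as per protocol. The protocol does not say how such a participant is classed, and that detail is commonly left to the analysis plan. It is something to state in advance, not an error.

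**A complier analysis has its own weakness.** Someone with two modules or three PM+ sessions counts as non-adherent yet received some treatment, which strains the exclusion restriction. Plain two-stage least squares on complete cases also would not keep all randomised participants under 30% attrition. Both points stand and shape the fix.

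**Conclusion.** The concern holds for the per-protocol analysis as written. Its membership rule acts on one arm and depends on post-randomisation distress, so the baseline-adjusted contrast tends to favour the programme under no effect. The size is modest: about 0.01 to 0.13 SD when attendance is unrelated to outcome, and 0.12 to 0.19 SD in the two cases examined where better-off participants attend more. It is near zero or reversed if the more distressed attend clearly more. These figures rest on assumed step-up shares, completion rates and correlations; only the structure of the rule can be read from the protocol. It should be corrected because the analysis is planned for primary and secondary outcomes, but it does not touch the main conclusion.

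**What to change.** 1. Label the per-protocol contrast descriptive and draw no effectiveness claim from it. This costs one sentence.
2. If the effect in adherers is of interest, estimate a complier-average causal effect with randomisation as instrument, adherence as the plan defines it, and adjustment for baseline PHQ-ADS. Analyse both arms as randomised, and handle missing t4 values under the same missing-at-random assumption as the main model, not by complete-case two-stage least squares. One simple form divides the mixed-model intention-to-treat difference at t4 by the adherent proportion in the intervention arm. If the intention-to-treat effect is zero, so is this estimate.
3. State in advance that participants with a missing t2 K10 and no PM+ are coded non-adherent.
4. Add a sensitivity analysis with a lower adherence threshold (any module started), because partial attendance can violate the exclusion restriction and inflate a real benefit.

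The cost is analysis-plan wording and a short piece of code; no new data are needed. The price is precision. With 70% DWM completion, s = 0.7 and a = 0.5, the adherent share is 0.70 × 0.65 = 0.455 (about 48 of 106). The interval is then roughly 1/0.455 = 2.2 times as wide as the intention-to-treat interval.
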